### Outcomes

Therapeutic effect:VAS of nasal symptoms score [14]

The scale includes overall nasal symptoms and differentiated nasal symptoms. The highest score for each section is 10, representing a symptom that is unbearable; the lowest score for each section is 0, representing a symptom with no influence. VAS score is accurate to one decimal place. It is used to evaluate the influence of overall nasal symptoms and differentiated nasal symptoms over the past week.

Data will be collected before the start of treatment (the baseline assessment) and at the end of each week during the treatment and follow-up periods.2.Rhinoconjunctivitis Quality of Life Questionnaire score [15]

The Rhinoconjunctivitis Quality of Life Questionnaire (RQLQ) includes 24 questions in seven sections: activity, sleeping, symptoms unrelated to nose and eyes, actual problems, nasal symptoms, ocular symptoms, and emotion. The score for each question is divided into seven levels: 0 = no influence, 1 = almost no influence, 2 = some influence, 3 = moderate influence, 4 = bad influence, 5 = worse influence, 6 = worst influence. The score is calculated separately in each section and the total score of these seven sections is considered as the RQLQ score. The highest possible score is 144. The scale is used to evaluate the influence of rhinitis symptoms on patient quality of life.

Data will be collected before the start of treatment (the baseline assessment) and at the end of each week during the treatment and follow-up periods.

The experimental indexes are serum CRH, plasma ACTH, cortisol, serum IL-4, and IFN-γ.

Data will be collected before the start of treatment (the baseline assessment), at the end of treatment, and 4 weeks after the treatment.

### Adverse events

Information on adverse events will mainly depend on the conscious feedback of individuals. Prior guidance is necessary for all volunteers. If an adverse event occurs, physicians will check the patients’ condition immediately and decide if any necessary examinations and treatments will be carried out. For serious adverse events, the trial will be interrupted immediately and proper steps will be taken, and detailed information on incidents will be recorded at the same time.

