### Planned interventions

#### Acupuncture treatment

Individuals from the observation groups will undergo either the acupuncture therapy or acupuncture with conventional treatment.Acupoints: Bai Hui (DU20), Yin Tang (EX-HN3), Ying Xiang (LI20), Tai Chong (LR3), He Gu (LI4), Zu San Li (ST36); Da Zhui (DU14), Fei Shu (BL13), Pi Shu (BL20), Gan Shu (BL18), Shen Shu (BL23).Needles: “Andy” disposable sterile stainless needles, size of 0.25 × 40 mmAcupuncture methods: All acupoints are positioned according to the People’s Republic of China, State Standard Name and Location of Acupoints (GB 12346–2006) [12]. In the prone position, Da Zhui (DU14), Fei Shu (BL13), Pi Shu (BL20), Gan Shu (BL18), Shen Shu (BL23) are punctured. Once all acupoints achieve “deqi” (an irradiation feeling deemed to indicate effective needling), stimulation of the needles is manipulated in balancing moves (reinforcing-reducing method) for 30 s. Acupuncture treatments last for 20 min. In the supine position, Bai Hui (DU20), Yin Tang (EX-HN3), Ying Xiang (LI20), Tai Chong (LR3), He Gu (LI4), Zu San Li (ST36) are punctured. Once all acupoints achieve “deqi”, stimulation of the needles is manipulated in balancing moves (reinforcing-reducing method) for 30 s. Acupuncture treatments last for 20 min.

Mind-regulating acupuncture treatment is done with patients in both the prone and supine positions, whereas conventional acupuncture is done only in the supine position.

Acupuncture is carried out thrice a week and lasts for 8 weeks, for a total of 24 treatments in each group.

The western medicine treatment in the two acupuncture groups is the same as that in the western medicine group.

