#### Western medicine treatment

Individuals in the control group will receive western medicine treatment.

According to the guidelines for the treatment of AR recommended by ARIA in 2008 [13], individuals in the control group will receive 2–4 weeks of intranasal corticosteroids, H1-antihistamines, or leukotriene receptor antagonists; after this, a specialized ENT examination will be repeated. An otolaryngologist will adjust the dosage or drug schedule according to the ENT findings, and treatments will be continued. One treatment course will last for 8 weeks.

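### Adverse events rest mainly on volunteered reports, and the acupuncture arms have 24 treatment sessions that the western-medicine arm lacks, so ascertainment may differ by arm

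*Protocol article*

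**What the plan says.** All references are to the protocol article.

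- **Adverse events:** "Information on adverse events will mainly depend on the conscious feedback of individuals". The next sentence adds that "Prior guidance is necessary for all volunteers". The physician's role begins once something has been reported: "If an adverse event occurs, physicians will check the patients’ condition immediately".
- **Acupuncture treatment:** "Acupuncture is carried out thrice a week and lasts for 8 weeks, for a total of 24 treatments in each group". The same section says that "The western medicine treatment in the two acupuncture groups is the same as that in the western medicine group".
- **Western medicine treatment:** 2–4 weeks of drug treatment, and "after this, a specialized ENT examination will be repeated". Treatment then continues to 8 weeks. The number of later visits is not given.
- **Outcomes:** VAS and RQLQ are collected at baseline and "at the end of each week during the treatment and follow-up periods", with no restriction by arm. Blood is taken at baseline, at the end of treatment and 4 weeks later. Whether the weekly scores are taken in clinic or at home is not stated.
- **Randomization and blinding:** participants and physicians are not blinded. Those who collect, evaluate and analyse the data are.

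**The concern.** When adverse events are recorded because a participant chooses to mention them, the chance of recording depends on how often that participant meets someone to tell. Here that frequency is tied to the randomized treatment. A participant on acupuncture meets a treating physician three times a week for 8 weeks; a participant on western medicine alone does not. Because allocation is open, expectations about needling or drugs may also shape what is mentioned and noted.

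If that happens, a difference in recorded events between acupuncture and western medicine would mix true risk with opportunity to report. The article's Background presents low toxicity and few side effects as an advantage of acupuncture, so readers are likely to look at these counts. Its Statistical analysis section provides chi-square or non-parametric tests between groups for count data. It does not name adverse events there, but event counts would be tested that way if they were compared. Events not captured during the trial cannot be recovered at analysis.

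**Working it through.** **1. The stated figure.** 3 sessions per week × 8 weeks = 24, as the article says. Because the drug treatment is the same in all arms, these sessions are wholly additional.

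**2. Contacts in the 8 treatment weeks.** The shared weekly assessments number 8 during treatment (and 4 in follow-up, 12 in all after baseline). Their mode is not stated, so three readings are shown.

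| Reading | Each acupuncture arm | Western medicine | Ratio |
|---|---|---|---|
| Weekly scores are staff contacts and coincide with sessions | 24 | 8 | 24/8 = 3.0 |
| Weekly scores are separate staff contacts | 24 + 8 = 32 | 8 | 32/8 = 4.0 |
| Scores completed at home; one ENT re-examination and one end-of-treatment blood draw | 24 + 2 = 26 | 2 | 26/2 = 13 |

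The first two rows assume that the ENT examination and blood draw fall on days already counted. If they are separate visits in every arm, the first row becomes 26/10 = 2.6. Further drug reviews in all arms would lower the third row. The surplus is at least 24 − 8 = 16 contacts on any of these readings. In the 4-week follow-up the stated schedule is the same in all arms.

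**3. Is any shared contact an adverse-event enquiry?** As described, VAS rates nasal symptoms, RQLQ rates the influence of rhinitis on quality of life, and the ENT examination serves drug adjustment. The guidance comes beforehand, and the physician's check follows a known event. None is described as a scheduled question about adverse events.

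**4. What unequal detection would do.** The article gives no event rate and no detection probability, so these inputs are assumed. Let p be the true risk, equal in both arms, and d the probability that an event is recorded. Then:

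- expected recorded events per arm = n × p × d
- observed ratio = d(acupuncture) / d(western medicine), whatever p is

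Take n = 108/3 = 36 per arm (Sample size section, 1:1:1 allocation), one acupuncture arm against western medicine, and a two-sided 5% test of two proportions by normal approximation (the article does not state sidedness). The last column is the chance of a significant excess under acupuncture although the true risks are equal.

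| p | d, acupuncture v western medicine | Expected records | Ratio | Chance of P<0.05 |
|---|---|---|---|---|
| any | 0.9 v 0.9 | equal | 1.00 | no bias |
| 20% | 0.9 v 0.7 | 6.5 v 5.0 | 1.29 | about 7% |
| 20% | 0.9 v 0.5 | 6.5 v 3.6 | 1.80 | about 16% |
| 50% | 0.9 v 0.5 | 16.2 v 9.0 | 1.80 | about 43% |

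For example, 36 × 0.20 × 0.9 = 6.5 and 36 × 0.20 × 0.5 = 3.6. At event risks of 20% the main effect is a distorted ratio rather than a likely false significant result.

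**The case against.** The strongest reply has four parts.

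- **The western-medicine arm is not out of contact.** It has the same 12 weekly assessments, blood draws and ENT re-examination, and the same prior guidance. This stands. It rules out the reading, which a reader might draw from the 24 sessions, that these patients are seen only two or three times. A harsher illustration built on that reading, say 80% against 30% of events recorded at a true risk of 20%, would give 0.20 × 0.80 = 16% against 0.20 × 0.30 = 6%. That is one extreme assumed pair and should not be used as the size of the problem.
- **A reader might infer that events under western medicine are in fact under-counted and that acupuncture will look less safe than it is.** The documents do not show this. They give no rates and no detection probabilities. The direction is plausible, no more.
- **The article condenses a fuller protocol.** The wording of enquiries and the content of case report forms may lie elsewhere, the schedule figure (Fig. 2) was not readable here and may carry an adverse-event row, and the word mainly leaves room for other sources. This limits what can be said about absence. It does not touch the point, which rests on a method the article states positively: volunteered report is the main source.
- **Safety is not a named objective.** The trial is described as exploratory and mechanistic, and no between-arm test of adverse events is specified. This lowers the weight of the point. The comparison of the two acupuncture arms is also unaffected by session count, since both have 24.

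**Conclusion.** The concern holds as a risk of differential ascertainment between each acupuncture arm and western medicine alone, confined to the 8 treatment weeks. It rests on three stated facts: volunteered report as the main source, 24 additional sessions in the acupuncture arms only, and open allocation for participants and physicians. The contact imbalance is about 3:1 at the low end and about 13:1 if the weekly scores are completed at home.

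The resulting bias cannot be sized from the documents. Under the assumed detection range, the observed event ratio at equal true risk lies between 1.0 and 1.8. Importance is moderate: the remedy is worth making because it is cheap and cannot be applied afterwards, but the main objectives do not depend on it.

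**What to change.** Add one fixed adverse-event question, worded identically for every arm, to the weekly VAS/RQLQ assessment in weeks 1 to 12 (8 treatment weeks and 4 follow-up weeks). Base any between-arm comparison of adverse events on these solicited answers. List events volunteered at acupuncture sessions separately, so that nothing is lost and the extra sessions do not enter the comparison. If the full protocol or the schedule figure already contains such an enquiry, say so in the Adverse events section.

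The cost is one extra line on a form already collected in every arm, and slightly more minor events recorded. No visit is added and no treatment changes. One practical point: an answer that mentions needling could reveal the allocation, so the line should be kept from the blinded outcome evaluators.

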### Sample size

This study is exploratory research designed to investigate the mechanism of acupuncture treatment for AR patients. With reference to the first stage of the clinical trial in the national drug register published in 2005, also based on a preliminary study and other research findings, the required sample size is 90; taking into account a 20% drop-out rate, a total of 108 cases will be recruited. Dongzhimen Hospital and Beijing Chaoyang Hospital are each responsible for 50% of recruitment for the clinical study. Another 36 healthy volunteers will be recruited as the control group, for a total of 144 cases.

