### Randomization and blinding

Using SAS 9.3.1 software (SAS Institute Inc., Cary, NC, USA), selected cases will be distributed in a 1:1:1 ratio to generate a randomized grouping table. Envelopes for the randomized grouping table will be prepared; the envelopes used are opaque, numbered in order, and contain the randomized serial numbers for grouping. According to the randomized serial numbers, individuals will be distributed to the observation groups and control group.

Researchers in charge of data collection, data statistics, and data evaluation will be blinded from the group allocation. However, individuals being treated and the physicians will not be blinded from the group allocation due to the different interventions in this trial.

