### Statistical analysis

Data from this clinical trial will be analyzed using SPSS version 21.0 software (released 2012, IBM Corp., Armonk, NY, USA). Demographic (age, sex, course, family history, et al.) and clinical data will be used as the baseline assessment to compare the two groups. The main and second indexes of therapeutic effects will be measured as mean ± standard deviation. Differences before and after the treatment in each group will be compared by paired *t*-test. ANOVA will be used in the comparison between groups. Count data will be measured by constituent ratio while chi-square test or non-parametric test will be used in the comparison between groups. *P*<0.05 indicates the difference is statistically significant.

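### The recruitment target of 108 matches 90 × 1.20, so at the plan's own 20% drop-out about 86 patients remain, about 4 short of the stated 90

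*Protocol article*

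**What the plan says.** The Sample size section of the protocol article gives a requirement, an allowance and a target in one sentence: "the required sample size is 90; taking into account a 20% drop-out rate, a total of 108 cases will be recruited". It divides recruitment equally between the two hospitals. It then adds a separate group: "Another 36 healthy volunteers will be recruited as the control group, for a total of 144 cases".

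The Randomization and blinding section supplies the allocation: "selected cases will be distributed in a 1:1:1 ratio to generate a randomized grouping table". With three arms, 90 is 30 per arm and 108 is 36 per arm. That section contains no error on this point and is used only for the ratio.

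The Sample size section calls the study exploratory. It attributes the 90 to a regulatory reference, a preliminary study and other research, and it states no effect size, standard deviation or power.

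**The concern.** A drop-out allowance should make recruitment large enough that the required number is still there after the expected loss. Because the loss is a fraction of those recruited, the requirement has to be divided by the fraction retained. Multiplying the requirement by one plus the drop-out rate gives a smaller number, and the target is then missed at the very rate it was meant to cover.

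The stated 108 fits the multiplication and not the division. What is at stake is whether the sentence tells readers correctly how many patients to expect at the end of the trial. As printed, it implies that 90 will remain after 20% drop out, and they will not.

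**Working it through.** **Inputs, all from the protocol article**
- Required number: 90 (Sample size), 30 per arm
- Drop-out rate: 20% (Sample size)
- Recruitment target: 108 (Sample size), 36 per arm
- Allocation: 1:1:1 (Randomization and blinding)
- Healthy volunteers: 36, in addition to the 108, for a total of 144 (Sample size)

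**Step 1. Reproduce the plan's figure.** Requirement × (1 + rate) = 90 × 1.20 = 108, an exact match. Per arm: 30 × 1.20 = 36.

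**Step 2. Apply the rate to those recruited.** Requirement / (1 − rate) = 90 / 0.80 = 112.5, rounded up to 113. Per arm: 30 / 0.80 = 37.5, rounded up to 38, so 3 × 38 = 114 for equal arms. The stated 108 is 5 to 6 patients below these figures, and no rounding of 112.5 gives 108.

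**Step 3. What 108 yields at 20% drop-out.** 108 × (1 − 0.20) = 86.4 in total and 36 × 0.80 = 28.8 per arm. The shortfall is 90 − 86.4 = 3.6 patients, and 3.6 / 90 = 4%.

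**Step 4. The drop-out that 108 does cover.** 1 − 90/108 = 18/108 = 16.7%.

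**Step 5. Chance of reaching 90.** If each of the 108 patients drops out independently with probability 0.20 (an assumption made here, not one in the plan), the probability that at least 90 remain is about 23%.

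**Step 6. Can the other group fill the gap?** 108 + 36 = 144, so the healthy volunteers lie outside the 108 and cannot replace patients with allergic rhinitis who leave.

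**The case against.** The strongest case on the other side is that this hardly matters. The gap is about 1.2 patients per arm, the study is labelled exploratory, and no arm, test or estimate changes. The Discussion itself concedes that the sample size should be improved in future. All of this stands as an argument about importance. It does not reconcile the three numbers, and the same sentence still presents 90 as required.

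A second objection is that the 20% might have been meant as a margin added to 90. The text calls it a drop-out rate, and losing 18 of 108 is 16.7%. If a margin was intended, the wording is what needs correcting.

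A third objection is that the article does not say that the 90 must be completers, and it defines no analysis set. Nasal symptom and quality-of-life scores are collected weekly, so a patient who leaves late may still contribute to those outcomes. That is fair. It carries less weight for the hormone and cytokine measures, which after baseline are taken only at the end of treatment and 4 weeks later. Reading the 90 as the number left after drop-out remains the natural meaning of such an allowance.

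It is also fair that the document prints no formula. One can say that 108 matches 90 × 1.20, not that it is known to have been computed that way.

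In the other direction, a reader might infer that the trial is underpowered or misses a power target. The document does not support that. It states no power to miss, and its between-group analysis is ANOVA, so a detectable difference worked out from a pairwise test at a chosen power would rest on inputs from outside the plan.

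**Conclusion.** The point holds as a minor arithmetic correction: the sentence is wrong as written. At the stated 20% drop-out, 108 recruited patients leave about 86 (28–29 per arm), about 4 (4%) fewer than 90. The target protects 90 only up to 16.7% drop-out.

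This rests on two readings: that the 20% is a fraction of those recruited, and that the 90 is the number wanted after drop-out. It does not depend on whether 90 was itself a sound choice, which cannot be checked from the document. The effect on power cannot be computed. A reader might also infer that more patients must be recruited. That does not follow, since stating the expected yield of 108 correctly resolves the inconsistency.

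**What to change.** Replace the sentence in the Sample size section with wording such as:

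> With 108 randomised (36 per arm) and 20% drop-out, about 86 patients (28–29 per arm) are expected to complete; 90 are reached only if drop-out is at most 16.7%.

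This costs one sentence and no patients. The expected size simply reads slightly less favourably. No statement of power or detectable difference is requested.

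For reference, if the sponsor prefers to keep 90 together with a 20% drop-out rate, the consistent recruitment figure is 113, or 114 for equal arms (38 per arm; 57 per hospital under the equal split). The overall total would then be 114 + 36 = 150, assuming that the healthy group stays at 36. The document does not say whether that 36 was chosen to equal the current arm size. If it was, a matching group of 38 would make the total 114 + 38 = 152.

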### Statistical analysis

Data from this clinical trial will be analyzed using SPSS version 21.0 software (released 2012, IBM Corp., Armonk, NY, USA). Demographic (age, sex, course, family history, et al.) and clinical data will be used as the baseline assessment to compare the two groups. The main and second indexes of therapeutic effects will be measured as mean ± standard deviation. Differences before and after the treatment in each group will be compared by paired *t*-test. ANOVA will be used in the comparison between groups. Count data will be measured by constituent ratio while chi-square test or non-parametric test will be used in the comparison between groups. *P*<0.05 indicates the difference is statistically significant.

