## Background

The impact of allergic rhinitis (AR) is not limited to nasal symptoms. Based on previous studies, AR results in severe dyssomnia which causes a lack of energy during the day. This seriously affects the quality of life and work efficiency of AR patients. In adition, AR has negative impacts on the learning capability, attention, and behavior of children [1]. AR patients experience various unpleasant emotions and conditions, for example, fatigue, anxiety, tension, depression, and low sensibility [2]. A recent study about patients with persistent AR reported that 74% of 166 patients experienced psychological stress. Another study [3] found that the synthesis and secretion of cytokines such as interleukin (IL)-2, IL-6 and interferon (IFN)-γ are induced by psychological stress [4]. Psychological stress leads to imbalance of two groups of T helper cells, Th1 and Th2. The increase in Th2 causes the body to be more susceptible to allergens. Therefore, the initiation of AR includes both biological (allergen) and mental (stress, anxiety, and depression) factors.

At present, conventional medicine treatments can relieve the nasal symptoms of AR effectively. However, the psychology of AR patients is not being addressed by physicians. Attention to the psychological state of AR patients is insufficient and treatment regarding patients’ psychological states is not considered during regular treatment by most ear-nose-throat doctors. This limits the therapeutic effects of the treatments [5]. Clinical research found that the negative emotions of AR patients could be relieved if the acupoints responsible for the depression are relieved and tranquilization is used at the base of regular acupoints. As well as effective relief of the clinical symptoms, quality of life was clearly improved [6]. At the same time, due to the low toxicity and side effects, compliance with treatments increases. However, current research regarding the mechanism by which acupuncture regulates AR is limited. Besides, the index used in most research is mostly restricted to the inflammatory cells and cytokines. This results in a lack of a systemic and integral research approach.

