### Recruitment

Volunteers come through public notices and are AR patients of Dongzhimen Hospital Affiliated to Beijing University of Chinese Medicine, Beijing Chaoyang Hospital and community hospitals. After selections, volunteers who satisfy all requirements are required to sign the informed consent. These volunteers will undergo one week of assessment and they are required to fill in the VAS forms on nasal symptoms. After one week, volunteers with a mean Visual Analogue Scale (VAS) of nasal symptoms score of 4 or above for 7 days are selected for this clinical trial. They are required to examine the level of corticotropin releasing hormone (CRH), adreno-corticotropic hormone (ACTH), cortisol (CORT), IL-4, and IFN-γ in the blood. Volunteers who are not eligible are provided regular treatments for 4 weeks.

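### Within-arm before/after paired t-tests carry an unrestricted P<0.05 rule, but all arms receive the same western medicine, so these P values cannot support a claim about acupuncture

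*Protocol article*

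**What the plan says.** The Statistical analysis section of the protocol article first says how the therapeutic outcomes are summarised: "The main and second indexes of therapeutic effects will be measured as mean ± standard deviation". The next sentence plans the within-arm test: "Differences before and after the treatment in each group will be compared by paired" t-test. The one after plans the between-arm test: "ANOVA will be used in the comparison between groups". A single criterion closes the section: P "<0.05 indicates the difference is statistically significant". Nothing ranks the paired tests below the ANOVA, and nothing says whether the ANOVA is run on change or on post-treatment values.

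Three other parts of the article decide what a before/after change means here:

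- **Treatment.** The Western medicine treatment section says that "individuals in the control group will receive 2–4 weeks of intranasal corticosteroids, H1-antihistamines, or leukotriene receptor antagonists", with treatment then continued to 8 weeks. The Acupuncture treatment section says: "The western medicine treatment in the two acupuncture groups is the same as that in the western medicine group". Trial design describes the arms in the same way.
- **Entry.** The exclusion criteria rule out antihistamines, steroids, decongestants and similar drugs within 14 days. Recruitment adds a symptom threshold: "volunteers with a mean Visual Analogue Scale (VAS) of nasal symptoms score of 4 or above for 7 days are selected".
- **Expected drug effect.** The Background says that "conventional medicine treatments can relieve the nasal symptoms of AR effectively".

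**The concern.** The baseline is taken off drug and the later assessments on drug, in every arm. A before/after change in an acupuncture arm is therefore the sum of the drug effect, natural course, some regression to the mean on VAS, and whatever acupuncture adds. A paired t-test asks only whether that sum is zero. It cannot separate the last component, which is the one the trial is about.

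The same problem reaches ACTH and cortisol, but conditionally. Intranasal corticosteroids are one of three listed drug classes, and the article does not say how many patients will receive them. To the extent that patients do, a within-arm hormone change mixes steroid exposure with any effect of acupuncture on the HPA axis.

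As the section stands, a significant paired test in an acupuncture arm and a null ANOVA would both be results under the same criterion, with no rule on which one answers the question.

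**Working it through.** **The plan's own figures.** The article gives no effect size, SD or correlation, so there is no planned figure to reproduce for this point. Allocation is 1:1:1. The required 90 gives 90/3 = 30 per arm, and the 108 recruited gives 108/3 = 36 per arm. I use n = 30.

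**Assumed inputs (not in the documents).** VAS in the source population is normal with mean μ = 5 or 6 and SD σ = 1.8. The before/after correlation is r = 0.6. A drug effect of 1 point is common to all arms, and the acupuncture effect is zero. The entry cut-off of 4 is from the article.

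**Step 1, regression to the mean.** With a = (4 − μ)/σ and λ = φ(a)/[1 − Φ(a)], selection raises the mean baseline by σλ, and (1 − r)σλ of that is lost on re-measurement.

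- μ = 5: a = −0.556, λ = 0.481, σλ = 0.866, fall = 0.4 × 0.866 = 0.35.
- μ = 6: a = −1.111, λ = 0.248, σλ = 0.447, fall = 0.4 × 0.447 = 0.18.

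**Step 2, total mean fall with the drug effect added.** 1.35 points (μ = 5) and 1.18 points (μ = 6).

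**Step 3, SD of the change.** Variance = (1 − r)² × Var(baseline | ≥4) + σ²(1 − r²), where Var(baseline | ≥4) = σ²(1 + aλ − λ²).

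- μ = 5: 0.16 × 1.624 + 2.074 = 2.334, SD 1.53.
- μ = 6: 0.16 × 2.146 + 2.074 = 2.417, SD 1.55.

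**Step 4, probability that the paired test reaches two-sided P<0.05.** The noncentral t has 29 degrees of freedom and noncentrality √30 × fall/SD.

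- μ = 5: 1.346/1.528 = 0.881, noncentrality 4.83, probability 99.7%.
- μ = 6: 1.179/1.555 = 0.758, noncentrality 4.15, probability 98.0%.

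**Step 5, simulation.** With 4,000 three-arm trials per setting under the same assumptions:

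| μ | Drug effect | Mean change | Each arm significant | All three significant | ANOVA on change rejects |
|---|---|---|---|---|---|
| 5 | 1 | −1.35 | 99.7% | 99.0% | 5.2% |
| 6 | 1 | −1.18 | 98.0% | 94.2% | 5.2% |
| 6 | 2 | −2.18 | 100% | 100% | 5.4% |

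**Step 6, what the entry threshold does alone.** With no drug effect, four settings (μ 5 or 6, SD 1.5 or 1.8, r 0.5 to 0.8) gave mean falls of 0.06 to 0.43 points and significance in 7% to 27% of arms. The shared drug treatment is the main driver; the threshold is a minor addition.

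**Step 7, what is left open in the between-arm test.** Randomisation protects an ANOVA on either change or post-treatment values from the bias above, so the open choice concerns precision and pre-specification. Under the same assumptions with μ = 5, the within-arm variance is 0.36 × 1.624 + 2.074 = 2.66 for post-treatment values, 2.33 for change and 2.07 after baseline adjustment. With μ = 6 it is 2.85, 2.42 and 2.07.

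**The case against.** The strongest reply is that the randomised question already has its test. The sentence after the paired t-tests plans a between-group ANOVA, the stated aim is to compare three groups, and ANOVA on change holds its 5% level in the calculation above. This stands, and it is the main reason for limiting the severity.

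A reader might infer more: that the trial will conclude efficacy from the paired tests, or will contrast arms by which of them reach P<0.05. The second practice would be misleading. If all three arms shared a true change of 0.5 SD, the paired test would have power p = 0.754 at n = 30, and some but not all arms would be significant with probability 1 − p³ − (1 − p)³ = 1 − 0.429 − 0.015 = 56%. But no sentence in the article assigns the paired tests either role, so this is a risk left open, not a planned analysis.

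Three further limits also stand:

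- The 14-day rule is an exclusion criterion; no washout is imposed.
- The expectation of a fall in every arm concerns symptom scores. The VAS threshold reaches hormones and cytokines only through any correlation with VAS.
- The 98.0% to 99.7% depends on the assumed 1-point drug effect. The article expects effective relief but gives no size.

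Within-arm change also has a proper use here, since the abstract plans to correlate changes in therapeutic and experimental indexes. Descriptive reporting preserves that.

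It could be added that a full analysis plan might label the paired tests descriptive. That may be so, but the tests and the unrestricted criterion are stated in the text, and the text is what needs the qualification.

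One opening phrase in the Acupuncture treatment section could be read as giving one observation group acupuncture without western medicine. It conflicts with the end of that section and with Trial design, and these should be reconciled. The argument here follows the latter two.

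**Conclusion.** The point holds at moderate severity. Within-arm P values cannot support a statement about acupuncture, because each arm's change includes a drug effect that all arms share. For ACTH and cortisol this holds to the extent that patients receive intranasal corticosteroids. Under the assumed values, a paired test on VAS is almost certain to be significant when acupuncture does nothing, whereas the between-arm comparison errs at its nominal rate. The reasoning needs only the shared treatment and the off-drug entry rule, both of which are in the article; the percentages are illustrative.

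It is not a fatal flaw. A between-group test is planned, the trial is described as exploratory, and removing the paired P values would leave the randomised comparison untouched.

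**What to change.** In the Statistical analysis section:

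1. Replace the paired t-tests with descriptive reporting of within-arm change: mean change with 95% CI, no inferential P value.
2. State that all efficacy and HPA conclusions rest on the between-arm comparison.
3. Specify that comparison as ANCOVA, with the post-treatment value as outcome, randomised arm as factor and the baseline value of the same measure as covariate. Report adjusted differences between arms with CIs.
4. Add one sentence saying that within-arm changes will not be used to claim an effect of acupuncture.

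The cost is analysis wording only. Baseline values are already collected for VAS, RQLQ and the laboratory markers, so no visit, sample or patient is added. What is lost is a set of P values that do not address the randomised question.
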